### Data analysis

The device data will be downloaded by the investigator and securely backed up locally as well as uploaded to the University of East Anglia’s secure research storage for permanent (tape backup) storage. The software will be used to convert the data from its encoded form on the SD card into the waveform samples provided by the device. The signals will then be resegmented into files, each file containing a full calendar day.

To train the algorithms, we require a collection of nystagmus waveform segments collected from a patient each labelled with the underlying diagnosis of the patient’s condition. The nystagmus waveforms from a patient’s data will be gathered by the computational team in two ways. First, by finding the positions of presses of the event marker in the signal and searching around these points for nystagmus-like signals; second by reading the patient’s diary entries and searching for signals at times when they have noted spells of dizziness (of course, these two conditions may often co-occur). Signals in these regions will be carefully assessed for possible evidence of nystagmus and any candidate waveforms will be copied and stored. Any relevant comments by the patient will be copied and stored with the accompanying waveforms. We will also use automatic analysis. We have already developed algorithms that can detect nystagmus-like waveforms with high accuracy and these will be used to both verify any waveforms found by the procedure above and to discover any other nystagmus events that the patient was either unaware of or had not marked.

After confirmation of nystagmus waveforms associated with the three target conditions of the study, algorithms will be built and tested to do automatic diagnosis. The most suitable computational technique for this task is machine learning (ML), sometimes known as ‘AI’. When using ML to make classifications, we aim to make maximum use of the available labelled data without falling into the trap of testing on material that is either part of the training set or is correlated with it which could lead to optimistically biased results. Hence the paradigm used here is to train on all the data except for that from a single subject and then test on that subject’s data. This procedure is repeated for each subject in turn and the average error rate and its SD are estimated. This technique is known as cross-validation.

An ML algorithm learns how to adjust automatically its parameters in such a way that it will make measurements on the waveforms that maximise the classification accuracy on the three diseases. Although it would not be obvious what these measurements are, it is possible to analyse the final ML model in such a way that we can later understand what the important criteria for distinguishing between the three diseases are. However, this process requires adequate data. If there is not enough data for the algorithm to learn the correct measurements, we can ‘help’ it by providing it with automatic measurements of features that we think may be important such as slow and fast phase velocities and amplitudes and measured nystagmus frequencies. We are in the process of incorporating these parameters.

Automatic diagnosis tests will be run periodically throughout the active stage of the project to identify potential problems in the data and to check that diagnosis accuracy continues to improve as more data becomes available. The final reported results will represent the diagnostic success rate of the project. The data should prove to be a rich source for further analysis that may considerably increase our understanding of the three target conditions and related matters.

A data validation plan will be developed to describe the downloading, storage and validation of the data in more detail and a statistical analysis plan will be finalised before analysis of the data.

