### Outcomes

#### Primary outcome

The primary outcome will be nystagmus identification using the algorithm. This will be derived for each participant by comparing the actual nystagmus data and the device-derived nystagmus data. Data will be collated to calculate an overall value for sensitivity and specificity for all participants.

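### On the natural reading, the nystagmus reference is verified and extended by the team's own detectors, so it is not independent of the software being scored

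*Protocol article*

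**What the plan says.** Under Outcomes, Primary outcome, the Protocol article states: "The primary outcome will be nystagmus identification using the algorithm". The outcome is derived for each participant by "comparing the actual nystagmus data and the device-derived nystagmus data", and then: "Data will be collated to calculate an overall value for sensitivity and specificity for all participants". That section does not say where the actual data come from.

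The Data analysis section is the only place that describes how nystagmus is established:

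- **Search.** "The nystagmus waveforms from a patient’s data will be gathered by the computational team in two ways": around event-marker presses, and at times of dizziness noted in the diary.
- **Human review.** "Signals in these regions will be carefully assessed for possible evidence of nystagmus and any candidate waveforms will be copied and stored".
- **Detectors.** The section says "We have already developed algorithms that can detect nystagmus-like waveforms with high accuracy" and that "these will be used to both verify any waveforms found by the procedure above and to discover any other nystagmus events", meaning events the patient did not notice or did not mark.

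The diagnostic algorithms are built after the waveforms have been confirmed. The section introduces the collection as training material: "To train the algorithms, we require a collection of nystagmus waveform segments collected from a patient each labelled with the underlying diagnosis". No second recording method is described, and no reader kept unaware of detector output. The Blinding section nevertheless calls the primary outcome objectively assessed.

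**The concern.** A reference standard should be settled without the test it is used to judge. Here the investigators' own detection software has two roles in settling it: it checks what the human search found, and it adds what the human search did not find. Each role can bias the result.

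- If a human-found event is discarded because a detector does not confirm it, a miss disappears from the sensitivity denominator.
- If a detector-found event is accepted, a false alarm can become a true positive, and specificity loses a false positive.

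Human search is confined to marked and diary regions. Elsewhere the detectors are the only search described, and no human-labelled negatives are described for that time.

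What is at stake is the stated primary outcome. The Data analysis section itself warns against optimistic bias from testing on material related to the training set. Its safeguard, leaving one subject out at a time, protects the diagnosis classifier from train/test overlap. It does nothing to make the nystagmus labels independent of the detectors.

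**Working it through.** The article gives no accuracy figure for nystagmus identification, so there is none to reproduce. Every input below is assumed and serves only to show how the mechanism behaves.

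**A. Detector events are only added.** Let s be the true sensitivity of the algorithm and h the share of true events found by human search. Assume that the adding detector is the scored algorithm, that all additions are true events, and that human and algorithm errors are independent. The reference then holds every event found by either, a share 1 − (1−h)(1−s) of all true events, of which the algorithm found s:

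apparent sensitivity = s / [1 − (1−h)(1−s)]

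| s | h | Calculation | Apparent | Change (points) |
|---|---|---|---|---|
| 0.80 | 0.90 | 0.80 / 0.98 | 81.6% | +1.6 |
| 0.80 | 0.70 | 0.80 / 0.94 | 85.1% | +5.1 |
| 0.80 | 0.50 | 0.80 / 0.90 | 88.9% | +8.9 |
| 0.95 | 0.70 | 0.95 / 0.985 | 96.4% | +1.4 |
| 0.95 | 0.50 | 0.95 / 0.975 | 97.4% | +2.4 |

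**B. Verifying and adding, taken apart.** Assume perfect human review, the same algorithm in both roles, true sensitivity 80%, true specificity 90%, and nystagmus in 5% of segments. Per 1,000 segments there are 40 true positives, 10 misses, 95 false alarms and 855 true negatives.

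- **Veto only** (every unverified event dropped): the 10 misses become negatives. Sensitivity 40/40 = 100%; specificity 865/960 = 90.1%.
- **Add only** (every detector event accepted): the 95 false alarms become positives. Sensitivity 135/145 = 93.1%; specificity 855/855 = 100%.
- **Both in full:** sensitivity 135/135 and specificity 865/865, both 100%.
- **A quarter of disagreements settled the detector's way:** sensitivity 63.75/71.25 = 89.5%; specificity 857.5/928.75 = 92.3%.
- **Half settled that way:** sensitivity 87.5/92.5 = 94.6%; specificity 860/907.5 = 94.8%.

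With nystagmus in 20% of segments (160, 40, 80 and 720), settling a quarter gives sensitivity 180/210 = 85.7% and specificity 730/790 = 92.4%. Settling half gives 200/220 = 90.9% and 740/780 = 94.9%.

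So the two roles act on different measures. A veto alone lifts sensitivity and leaves specificity almost unchanged. Both measures reach 100% only when one algorithm vetoes and adds in full.

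**The case against.** Much of the opposing case is right and limits the point.

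- **The link is inferred.** The waveform collection is introduced as training material and is never named as the actual nystagmus data of the primary outcome. That stands. But no other source is described, so this is the natural reading; if another reference exists, it needs naming.
- **The algorithms may differ.** The verifying detectors already exist, while The CAVA device section says the software will be developed from this trial's data. If they differ, the bias depends on how far their errors agree. False additions by one detector that the scored algorithm does not flag would even lower apparent sensitivity. That stands, and it is why no size can be fixed.
- **The handling rules are not given.** The article does not say whether an unverified waveform is dropped, or whether a discovered event is reviewed before acceptance. A reader might infer that accuracy must come out at 100%. That needs one algorithm and both rules in full, and the article states neither rule.
- **The 3% margin.** A reader might infer that the bias exceeds the trial's own margin. That margin, under Sample size, concerns diagnosis per condition. At that section's 95%, the illustration gives +1.4 to +2.4 points.
- **Negatives.** A reader might infer that there are none. Stretches that human review rejects within marked or diary regions could serve. The gap is unmarked time.
- **Deferred detail.** Validation and analysis are left to a data validation plan and an SAP. That would answer an omission. Here the article states a procedure in which detectors verify and add.

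**Conclusion.** The point holds in limited form. On the natural reading, the reference for the primary outcome is not independent of the team's detection software, and followed as written the plan lets detector output into it. This would usually inflate apparent sensitivity and specificity, to the extent that the scored algorithm shares the existing detectors' errors.

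The document does not allow the size to be computed. The illustrations run from about 1.5 points to about 9 points of sensitivity when events are only added, and to about 15 points (80% read as 94.6%) when half of all disagreements are settled the detector's way. They rest on the same algorithm in both roles and on assumed accuracy, prevalence and human detection.

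A reader might extend the point to diagnostic accuracy. The documents do not support that: the Intervention section compares the system's diagnosis with each patient's known diagnosis, which is a separate reference, and the Sample size section concerns that comparison.

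**What to change.** In the data validation plan and the SAP, define actual nystagmus for evaluation as human labels locked before any detector is run on that recording. The labels should cover:

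- the event-marker and diary regions, including stretches judged free of nystagmus; and
- a random sample of unmarked windows, read by the same team, to supply negatives from the rest of the recording.

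Compute sensitivity and specificity only against these locked labels. Detector output must neither remove a human label nor add to the reference set. Detector-found events may still be used for training, and should be reported separately from the accuracy results. If a different reference is already intended, name it and state that detector output does not enter it.

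The cost is a change in labelling order and some extra reading of sampled windows. Analysis is already off-line and the recordings are kept permanently, so no further recruitment or participant contact is needed.

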### Sample size

A minimum sample size of 85 participants for each of the three conditions is required to demonstrate a minimum diagnostic sensitivity of 95% and a specificity of 95% with a 3% margin of error for each condition.

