### Retention

The trial intervention period is relatively short, so retention is not expected to be too challenging. It is anticipated that some participants will not wear the CAVA device or have a dizziness attack while wearing the device within 30 days, so the sample size is inflated to allow for this. Some non-conformance will be apparent or self-reported by the participant, others will only be detected once the data is downloaded at the end of the 30 days. Therefore, recruitment will continue until the device data analysis team confirms 255 participants with one qualifying dizziness event or the maximum upper approved limit of 400 participants is reached.

A potential challenge with retention is participants who drop out not returning the CAVA device. As this could impact the rest of the trial, participants are offered a £20 voucher incentive on return of the device and electrodes.

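### The stated summary of the cross-validated diagnosis is one average error rate over all subjects, which cannot show whether the per-condition sensitivity and specificity behind the sample size are reached

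*Protocol article*

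**What the plan says.** The Sample size section of the protocol article sets the target by condition: "A minimum sample size of 85 participants for each of the three conditions is required" in order "to demonstrate a minimum diagnostic sensitivity of 95% and a specificity of 95% with a 3% margin of error for each condition".

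The Intervention section says that the algorithm will diagnose each patient from the device data and that accuracy will be tested against the patient's known diagnosis. The Data analysis section describes how: "train on all the data except for that from a single subject and then test on that subject’s data". It then gives the summary: "This procedure is repeated for each subject in turn and the average error rate and its SD are estimated". Later in the same section the final reported result is described as one diagnostic success rate for the project.

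No section names sensitivity or specificity for each condition, or a confidence interval, as an output of the diagnostic analysis. The Data analysis section also says that a statistical analysis plan will be completed before the data are analysed; it is not available here.

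**The concern.** The trial is sized on one kind of quantity and its diagnostic result is described by another. The target is a sensitivity and a specificity for each of Ménière's disease, vestibular migraine and benign paroxysmal positional vertigo. The described summary averages over every left-out subject, and so over all three conditions. Good performance in two conditions can then hide poor performance in the third.

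This matters because the Introduction says that the three conditions are treated differently, with different risks, so it matters which one is misclassified. The SD adds a second problem: a reader may take it as the error bar on the result, and the text does not say whether it is one.

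**Working it through.** **Inputs.** From the article: 85 participants per condition, 255 in total, target 95%, margin 3 points. Assumed for illustration: one right-or-wrong diagnosis per participant, an error rate near 5%, and the splits of errors shown below.

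**The plan's own figure.** The usual precision formula is n = z² p(1 − p)/d², with p = 0.95 and d = 0.03.
- At two-sided 95% confidence: 1.96² × 0.0475 / 0.0009 = 202.7, so 203 per condition.
- At two-sided 80% confidence: 1.2816² × 0.0475 / 0.0009 = 86.7, so 87 per condition.

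The article states no confidence level, and 85 is not reproduced at the conventional one. That is a separate matter. What counts here is that the target is per condition.

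**Does the average determine the per-condition figures?** Take 13 errors in 255, which is 13/255 = 5.1%. Sensitivity has denominator 85; one-versus-rest specificity has denominator 170.

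| | Errors spread 4, 4, 5 | All 13 in one condition |
|---|---|---|
| Average error | 5.1% | 5.1% |
| SD over 0/1 results | 0.220 | 0.220 |
| Sensitivities | 81/85 = 95.3%, 81/85 = 95.3%, 80/85 = 94.1% | 72/85 = 84.7%, 100%, 100% |
| Exact 95% CI, lowest sensitivity | 86.8% to 98.1% | 75.3% to 91.6% |
| Lowest specificity | 165/170 = 97.1% | 157/170 = 92.4% |

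The specificities assume that the wrong labels fall 4, 5, 4 across the conditions in the first case and all on one other condition in the second. The stated summary is identical in both columns. In the second, even the upper confidence limit for the weak condition is below 95%.

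**Does the mix of conditions matter?** With assumed sensitivities of 98%, 95% and 85%:
- at 115/85/55 participants, (115 × 0.02 + 85 × 0.05 + 55 × 0.15)/255 = 14.8/255 = 5.8%;
- at 55/85/115 participants, (55 × 0.02 + 85 × 0.05 + 115 × 0.15)/255 = 22.6/255 = 8.9%.

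So if the evaluable groups are not equal, the same classifier gives different averages.

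**What could the SD mean?** There are three readings.
1. *Spread over folds scored 0 or 1.* It is √(p(1 − p)), up to a factor √(n/(n − 1)). At p = 0.05 this is √0.0475 = 0.218, or 21.8 points, whether n is 85 or 255. It follows from the error rate and does not shrink as n grows.
2. *Spread between patients of waveform-level error rates.* This is a legitimate description of how patients vary, but it is not the precision of the estimate.
3. *Standard error of the average.* This is precision, but of the pooled rate: 0.218/√255 = 0.0136, or 1.4 points. For one condition it is 0.218/√85 = 0.0236, or 2.4 points, larger by √3.

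None of the three gives the precision of a per-condition estimate.

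**The case against.** The strongest reply is that the sentence in Data analysis explains a technique and does not lay down the trial's only reporting format. The average error rate and the per-condition sensitivities come from the same held-out predictions, so giving one does not exclude the other. Tables and interval methods are normal content for a statistical analysis plan, which is promised. With equal groups, overall accuracy is also the mean of the three sensitivities, a recognised summary.

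Much of this stands. A reader might infer that the plan excludes a breakdown by condition; the text does not say so. What remains is that the article does state a diagnostic summary, and speaks of the final result as a single rate, while justifying its size by something that this summary cannot show. That is a mismatch between stated passages and not mere silence.

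Two further inferences should be resisted. The first is that the SD is certainly no measure of precision. Grammatically, the SD may belong to the average, which makes it a standard error, and folds may be scored by waveform. The 21.8-point figure holds only for 0/1 folds. The second is that the Primary outcome section, which says "Data will be collated to calculate an overall value for sensitivity and specificity for all participants", proves that diagnostic results will be pooled. That sentence concerns identification of nystagmus, not classification of the three conditions, and is no evidence on this point.

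**Conclusion.** The concern holds in a limited form. The stated summary of the cross-validated diagnosis cannot show whether the per-condition target is met: a 5.1% average error is compatible with sensitivities of about 95% throughout or of 84.7% in one condition. The uneven split is an extreme illustration, not a forecast. The SD needs a definition, and even as a standard error it describes the pooled rate only.

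The conclusion assumes that the average runs over all subjects, as the text says. The figures assume one diagnosis per participant, 85 per condition and independent results between participants. The defect is one of wording and can be repaired without any change to design or data; the unseen analysis plan may already do so. It should be corrected, but it does not undermine the trial.

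**What to change.** In the Data analysis section, and in the statistical analysis plan, replace the summary sentence with text to this effect: *Each participant receives one cross-validated diagnosis. The 3x3 table of predicted against reference diagnosis is reported. For each condition, sensitivity (about 85 participants) and specificity against the other two conditions (about 170 participants) are given with exact or Wilson 95% confidence intervals, with the participant as the unit of analysis. The overall error rate is supplementary and has its own confidence interval.* Drop the SD, or state what it measures.

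This should be settled before data lock, since the article also plans periodic accuracy tests while the trial is active. The cost is wording and a few lines of analysis on predictions that will exist anyway. The downside is less favourable intervals. At a true 95%, the approximate 95% half-widths (1.96 times the standard error) are 4.6 points for a condition's sensitivity (n = 85) and 3.3 points for its specificity (n = 170), against 2.7 points for the pooled rate (n = 255).

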### The CAVA device

The CAVA system will eventually consist of two separate elements: Hardware and software. The software will be developed from the data collected from this trial and is not fully developed or under test in this trial.

The hardware is composed of two parts. First, there is a reusable device that sits over the ear and records eye and head movements; this is comprised of a logging module containing a battery, microcontroller, accelerometer, data storage facility, an event marker button and connection ports. Second, there are two single-use sensory arrays (electrodes) that adhere to the participant’s face (figure 1).The software will consist of a computer algorithm which will compute head and eye data recorded during a 30-day period. The data used to undertake this work will be uploaded onto a computer from an SD card stored in the device. This data analysis is performed ‘off-line’ after the participant has worn the device.

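### The final diagnostic accuracy is open to optimistic bias, because leaving out one subject does not guard against choosing the model on the same subjects

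*Protocol article*

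**What the plan says.** All of the following is in the protocol article.

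- **Validation scheme (Data analysis).** The team will "train on all the data except for that from a single subject and then test on that subject’s data". It adds: "This procedure is repeated for each subject in turn and the average error rate and its SD are estimated". The stated reason is to use the labelled data fully without "falling into the trap of testing on material that is either part of the training set or is correlated with it", which the section recognises would make results too optimistic.
- **Repeated tests (Data analysis).** "Automatic diagnosis tests will be run periodically throughout the active stage of the project". Two purposes are given: finding problems in the data, and checking that accuracy keeps rising as data accrue. Neither the number nor the timing of the tests is given.
- **Adaptable algorithm (Data analysis).** If the data are too few for the algorithm to learn the right measurements, the team can supply computed features such as phase velocities, amplitudes and frequencies. The section says these are already being built in.
- **Final result (Data analysis).** The final results are to stand as the project's success rate in diagnosis. No locked pipeline, nested loop or untouched test set is named.
- **Status of the software.** The CAVA device section says the software will be developed from this trial's data and "is not fully developed or under test in this trial". The Intervention section says the system's accuracy will be tested against each patient's known diagnosis.
- **Timing of the SAP.** Data analysis says "a statistical analysis plan will be finalised before analysis of the data". Ethics and dissemination places drafting and approval of the statistical analysis before data lock.

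**The concern.** Cross-validation gives an honest estimate for one fixed procedure. Suppose several procedures are scored by the same loop and the one that scored well is kept. Its score then includes the luck that made it look best. Each subject was left out of the fitting but took part in the choice.

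The article names the hazard of optimistic results, but the remedy it states covers only overlap or correlation between training and test material. It does not cover selection, and the conditions for selection are present: an algorithm still under development, hand-made features that may be added, and accuracy looked at repeatedly on accumulating subjects.

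The SAP's timing does not close the gap. The periodic tests are themselves analyses of diagnostic accuracy, and the Commercialisation section plans a public event on interim findings. A SAP approved just before data lock could therefore follow several looks at accuracy.

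The figure at stake is the diagnostic accuracy, for which the Sample size section sets a target of 95% sensitivity and 95% specificity with a 3% margin of error. Optimism approaching that margin would not show in a confidence interval, because it shifts the estimate and does not widen the interval.

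**Working it through.** **1. The plan's own figures.** The article gives no figure for optimism. The nearest benchmark is the 3-point margin at 95% (Sample size). The half-width is 1.96 × √(0.95 × 0.05 / n), taking 95% confidence as an assumption because no level is stated:

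- n = 255: 1.96 × √(0.0475/255) = 2.7 points.
- n = 85: 1.96 × √(0.0475/85) = 4.6 points.

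So the 3-point margin is met on the pooled 255 but is not reproduced for 85 per condition. That is a separate matter and does not decide this point.

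**2. Inputs for the optimism.**

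- From the article: n = 255 (3 × 85) and the planning accuracy of 95%.
- Assumed, because the article is silent: the number K of candidate pipelines compared, and the correlation ρ between candidates in whether a given subject is classified correctly.

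**3. Model.** All K candidates have the same true accuracy, so any gain from picking the best is pure optimism. Candidate k classifies subject i correctly if √ρ·sᵢ + √(1−ρ)·eᵢₖ < Φ⁻¹(0.95), with s and e standard normal. Optimism is the mean of (best observed accuracy − 0.95).

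**4. Check by hand with ρ = 0.** The standard error of one accuracy is √(0.0475/255) = 1.37 points. The expected maximum of K standard normals is 1.163 for K = 5 and 1.539 for K = 10. This gives 1.37 × 1.163 = 1.6 and 1.37 × 1.539 = 2.1 points. Simulation with ρ = 0 gives 1.6 and 2.0. Correlation lowers these values.

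**5. Simulation (4,000 runs per cell), optimism in points:**

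| Candidates compared | ρ = 0.8 | ρ = 0.5 | ρ = 0.3 |
|---|---|---|---|
| 1 (prespecified or nested) | 0.0 | 0.0 | 0.0 |
| Best of 2 | 0.6 | 0.7 | 0.7 |
| Best of 5 | 1.1 | 1.4 | 1.5 |
| Best of 10 | 1.5 | 1.8 | 1.9 |
| Best of 50 | 2.1 | 2.5 | 2.7 |

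Separate runs differ by less than 0.1 point.

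**6. Sensitivity for one condition.** The article describes one classifier for all three diseases. With 85 subjects per condition, overall accuracy is the mean of the three sensitivities. Choosing on overall accuracy therefore inflates each sensitivity, on average, by the overall amount. In the same simulation the inflation for one condition was 1.5 points for best of 5 and 1.9 for best of 10 at ρ = 0.3, in line with the table.

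**The case against.** The strongest reply is that nothing in the article says selection will occur. The stated purposes of the periodic tests are data problems and monitoring. The trigger for hand-made features is too little data, not low accuracy, and those features are already being incorporated. Slow phase velocity is also among the parameters that the Introduction takes from earlier proof-of-concept work. Nor does the article say that the periodic tests use the leave-one-subject-out loop. All of this stands. A reader might infer that the periodic tests steer the algorithm, or that the final figure is biased. The text supports neither as fact.

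Second, the simulated procedure may be harsher than the real one. The only choice the article names is with or without hand-made features, which is best of 2. Subjects added after the last test would not have influenced that choice. If it is made halfway through, the 0.6 to 0.7 points shrink by a factor of about √½, to 0.4 to 0.5. This also stands and favours the lower end of the range.

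Third, nested tuning and code freeze commonly belong in a SAP or full protocol, and neither is shown. This stands only in part. The article itself fixes the validation scheme as its protection against optimism, and that scheme is incomplete for the purpose. A SAP finalised after accuracy has been seen cannot undo earlier choices.

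Other stronger readings fail:

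- A larger inflation for a single condition would need a separate best pipeline for each condition, which is not what is described.
- Leakage through site or logging unit would need conditions to cluster by site or unit, which the article does not report.
- The Economic evaluation section does not say that the estimated accuracy enters the cost-effectiveness model.

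**Conclusion.** The point holds as a risk. The stated safeguard covers train/test overlap and not model choice, while the same subjects serve development, periodic accuracy tests and the final estimate. At 95% true accuracy and 255 subjects, the optimism runs from about 0.6 points (best of 2) to 2.7 points (best of 50), and is near zero if nothing is chosen on the data or if selection is nested. At the upper end it comes close to the planned 3-point margin; it does not exceed it at these settings. The range rests on assumed numbers of equally accurate candidates, all scored on the full sample, and on an assumed correlation of 0.3 to 0.8.

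It concerns the diagnostic classification. The primary outcome as worded under Outcomes is nystagmus identification, for which the article says detection algorithms already exist, and the calculation does not apply to it.

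The two descriptions of the software, as not under test and as having its accuracy tested, leave unclear whether the result is development or validation.

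**What to change.** - **Nest the selection.** Make every choice (hand-made features or not, architecture, hyperparameters, decision threshold) inside the training folds, and report only the results on the outer left-out subjects.
- **Restrict the periodic tests.** Use them for data quality only, or run accuracy on a fixed development subset.
- **Freeze early.** Fix the SAP and the selection procedure before the first full-data accuracy run. Log any change made after a periodic test, including tests already run, and report the log with the result.
- **Label the result.** Describe it as development with internal validation, and reconcile the CAVA device section with the Intervention section.
- **Optional.** Repeat the final run with folds grouped by site or logging unit as a sensitivity analysis.

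The cost is computing time, some wording, and a slightly less favourable reported accuracy. No extra participants are needed. The change should be made before the final accuracy is known, because the choices cannot be made blind to it afterwards.
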